### Data management and statistical analysis

All analyses will be conducted on an intention-to-treat basis. If there are chance imbalances in baseline participants’ characteristics, then these variables will be used as covariates. Mixed linear modelling incorporating intervention and control groups at the baseline and two follow up time points (18 weeks and 26 weeks after intervention commencement), with the number of sessions attended and baseline physical activity level as covariates, will be carried out using SPSS. Comparisons will be made for the primary outcome (BOOMER) and secondary outcomes (functional tasks, strength measures, gait parameters, health related quality of life measures, and psychosocial measures). Although the number of falls is being recorded over a period of 12 months after the commencement of participants, this study is not powered for falls outcomes. Regarding the qualitative data being collected, the interviews from EPIG participants will be analysed using a thematic analysis approach [55], as described above.

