The “exercise park for older people” was originally introduced in Europe in 2009 as a novel purpose-built exercise park designed to improve muscular strength, flexibility, coordination and balance through active fun activities. The exercise park aims to inspire older people to be playful, to exercise, and to challenge their bodies, which can lead to a more active and healthier life style. Such indoor and outdoor exercise parks are widely available in Finland, Spain and China with only few operating in Australia. Preliminary data from The Netherlands suggests the purpose-built exercise parks may be safe and acceptable to older people. However, no evidence-based research exists that demonstrates the effectiveness of the exercise park in improving physical health, psychological well-being or independence. A report from The Netherlands [15] provided preliminary evidence of the feasibility of a 10 weeks exercise program with the exercise park equipment for a small sample of older people (*n* = 13), reporting high attendance (92 %), reduction in fear of falling and increased muscle strength and balance. Although these results are promising, further research is needed with a larger sample size and a longer intervention period to determine the effectiveness of the exercise park program on physical and psychological outcomes, well-being and independence of older adults, as well as determining the feasibility and acceptability of this type of program in the Australian community.

Therefore, the aims of this study are (1) to evaluate the effectiveness of such an exercise park in reducing the risk of falls and (2) to evaluate what other benefits, including psychosocial, functional and physiological, can be achieved by using this specific exercise park for 18 weeks with a structured and progressive program in community dwelling older adults using a randomised controlled trial design and (3) what benefits are sustained eight weeks after completion of the exercise park program.

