### Design and setting

This study will be a parallel randomised controlled trial (RCT) with pre and post intervention design (outcome assessments at baseline and at 18 and 26 weeks after participation commencement) comparing an exercise park intervention program for older people with a control group, aiming at evaluating the effectiveness of an exercise intervention using an exercise park specifically designed for older people in reducing the risk of falls.

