### Recruitment and randomization

Participants will be recruited from Melbourne suburbs. Local senior organizations, retirement villages, community centres, senior clubs and associations in the areas around the park location will be contacted for recruitment purposes. Participants will be also recruited via community health promotion events and advertisement in local newspapers, magazines and online social networking media. Participants will be informed about the project by posters placed in healthcare facilities and places with high circulation of senior citizens and mail-out advertisements to health care practitioners in Melbourne. Participants will be randomly allocated to one of the following groups: (1) Exercise Park Intervention Group (EPIG) or (2) Control Group (CG). Block randomization stratification by gender will be undertaken, so that blocks of 12 participants will be recruited at a time, randomized into one control group of six participants and one exercise groups of six participants (Fig. 1). To accommodate couples (e.g. partners/married couples) participation, randomisation by couple will also take place. Assessors will prepare the envelopes with six paper codes (three exercise intervention and three control group) which will be added to opaque not concealed envelopes. There will be three envelopes: one for couples, one for females and one for males. Participants will be asked to pick one paper from their respective envelope and the picked paper will assign the participant to either the exercise intervention group or control group. Recruitment will be undertaken over a period of 14 months to achieve a sample size of 60 participants in each group. Assessors and participants will not be blinded to their respective group allocation (EPIG or CG).

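### The primary model takes its covariates from observed chance imbalance and leaves out the randomisation strata; fix the model in advance, and name the 18-week BOOMER contrast as primary

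*Protocol article*

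**What the plan says.** The analysis section of the protocol article sets out the model in three steps.

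- Covariate rule: "If there are chance imbalances in baseline participants’ characteristics, then these variables will be used as covariates". What counts as an imbalance, and which characteristics are eligible, is not stated.
- Model: "Mixed linear modelling incorporating intervention and control groups at the baseline and two follow up time points", "with the number of sessions attended and baseline physical activity level as covariates".
- Outcomes: "Comparisons will be made for the primary outcome (BOOMER) and secondary outcomes". No visit is attached to the primary outcome.

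Under Recruitment and randomization, "Block randomization stratification by gender will be undertaken", and "There will be three envelopes: one for couples, one for females and one for males". The allocation strata are therefore couples, single females and single males. None of them is named in the model.

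Design and setting gives "outcome assessments at baseline and at 18 and 26 weeks after participation commencement". The third aim in the Background asks "what benefits are sustained eight weeks after completion of the exercise park program", which ties 26 weeks to durability of benefit. The Limitations section says that the study is unblinded and that the principal researcher conducts assessment, randomisation and intervention.

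**The concern.** A rule driven by imbalance asks the wrong question of a covariate. It adjusts for variables that differ between arms whether or not they predict BOOMER, and it ignores predictive ones that happen to balance. Sex could enter only if it were imbalanced, which stratification is meant to prevent. Because imbalance is undefined, the choice of model is open to discretion once data are seen, in a trial without blinding.

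Two other parts of the same model are not pinned down. Baseline is one of the three modelled time points, but the text does not say whether the arms share a baseline mean. That decides whether the treatment contrast is a difference in change or a baseline-adjusted difference. And with two follow-up visits of equal standing, a claim could rest on either, while the sample size covers one comparison.

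**Working it through.** **Inputs.** From the Sample size section: effect size d = 0.5, alpha 0.05 (sidedness not stated), power 0.80, 48 per group, 20% dropout, 60 per group recruited. Assumed, because the article does not give them: a two-sided test; the correlation between baseline and follow-up BOOMER; the correlation of other covariates with BOOMER; an imbalance flag at p < 0.05; the correlation between the 18- and 26-week tests.

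**1. The plan's own figure.** Unadjusted and two-sided, n = 2(1.960 + 0.842)²/0.5² = 62.8, so 63 per group. One-sided, 2(1.645 + 0.842)²/0.5² = 49.5, so 50. With baseline adjustment at r = 0.5, 62.8 × (1 − 0.5²) = 47.1, so 48. Dropout: 48/0.8 = 60, as stated. Read as two-sided, the planned 48 needs some gain from baseline. Without it, power is Φ(0.5/√(2/48) − 1.960) = Φ(2.449 − 1.960) = 0.69.

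**2. The imbalance rule.** Simulation of a single follow-up with 48 per group and one normal covariate (100,000 trials per setting), adjusting only if the covariate differs between arms at p < 0.05:

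| Correlation with BOOMER | Power, rule | Power, always adjust | Type I error, rule |
|---|---|---|---|
| 0.2 | 0.678 | 0.691 | 4.9% |
| 0.3 | 0.683 | 0.716 | 4.7% |
| 0.5 | 0.688 | 0.795 | 4.4% |
| 0.7 | 0.696 | 0.921 | 3.6% |

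Always adjusting holds type I error at 4.9% to 5.0%. The rule therefore recovers almost none of the available precision, and it errs on the conservative side.

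If instead the more favourable of the adjusted and unadjusted results were reported for just one covariate, type I error would be about 7% at correlation 0.5 and 8% at 0.7. That is the cost of discretion if it were used.

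How often would the rule fire? For k independent characteristics at a 5% flag, the chance of at least one is 1 − 0.95^k: 40% for k = 10, 54% for 15, 64% for 20. The article states neither k nor the flag.

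**3. The strata.** Suppose sex explains a share R² of BOOMER variance and is balanced by design. The unadjusted test then has a true alpha of 2[1 − Φ(1.960/√(1 − R²))]: 0.049, 0.044 and 0.039 for R² = 1%, 5% and 10%. At 10%, power without adjustment is Φ(0.489/√0.9) = 0.70. With adjustment it is Φ(2.449/√0.9 − 1.960) = 0.73. The loss is at most about 4 points over this range.

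**4. Baseline BOOMER.** With outcome variance 1, a difference in change has variance 2(1 − r) per person. A baseline-adjusted difference, or a model with equal baseline means, has 1 − r². Power = Φ(0.5/√(2v/48) − 1.960), with v the relevant variance:

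| r | Change | Adjusted or constrained |
|---|---|---|
| 0.3 | 0.54 | 0.73 |
| 0.5 | 0.69 | 0.81 |
| 0.7 | 0.89 | 0.93 |
| 0.8 | 0.97 | 0.98 |

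Simulation with t-tests gives figures about one point lower: 0.68 against 0.80 at r = 0.5, and 0.88 against 0.92 at r = 0.7.

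**5. Two visits.** For two two-sided 5% tests with bivariate normal statistics, the chance that at least one rejects under no effect is 9.1%, 8.4% and 7.0% at between-test correlations of 0.5, 0.7 and 0.9.

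**The case against.** The strongest reply is that the power figures at correlations of 0.5 and 0.7 describe a covariate explaining 25% or 49% of BOOMER variance. The likeliest such variable is baseline BOOMER, which is already modelled, and baseline physical activity is already fixed. What the rule governs is mostly age, sex, education, medical history and the like, where a correlation of 0.2 to 0.3 is more plausible and the loss is about 1 to 3 points. That stands. It also means that the losses in steps 2 and 4 must not be added together.

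Three stronger readings are tempting, and the article does not support them.

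- A reader might infer that baseline BOOMER is left out. It is in the model as a response at the first time point. Whether anything is lost depends on a constraint the article does not state, which could be settled in a fuller plan.
- A reader might infer that the imbalance rule inflates type I error. Applied mechanically it lowers it; only discretionary use would raise it, and nothing shows that discretion is intended.
- A reader might infer that the missing primary visit costs power. It does not. It raises type I error, and only if success at either visit is accepted. The article nowhere says that it is, and the aims already point to 18 weeks for effectiveness and 26 weeks for durability. That is an order of intent, not a designation.

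The imbalance rule and the covariate list are different in kind. They are stated, not left out, so condensation into an article does not explain them.

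**Conclusion.** The point holds in limited form. The article states a data-dependent covariate rule without list or criterion, and its named covariates omit the randomisation strata. The harm is mainly lost precision with a conservative test: 1 to 3 power points for moderate covariates, about 11 for a strong one, and at most about 4 for a stratifier explaining up to 10% of variance. Undefined imbalance adds room for discretion.

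The handling of baseline BOOMER could cost nothing, or about 12 points at r = 0.5 (more at lower r, 4 to 5 at 0.7), and the article does not say which. The unnamed primary visit is an error-rate matter of about 7% to 9% if either visit counts.

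Every correlation and R² is an assumption. The directions are firm and the sizes are not. This is a worthwhile improvement that costs nothing in data; it does not show the trial to be invalid.

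**What to change.** Delete the imbalance sentence and state one primary model in advance:

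- Response and contrast: BOOMER, EPIG minus CG at 18 weeks, as the single primary test. The 26-week contrast is secondary and answers the third aim.
- Baseline BOOMER: either as a covariate, or as a response with baseline means constrained equal across arms.
- Other covariates: sex and couple status (together the randomisation strata) and baseline physical activity.
- Any adjustment prompted by observed imbalance: sensitivity analysis only.

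Say openly that the number of sessions attended is removed from the primary model. It is measured after randomisation, and the Feasibility section counts full adherence as 35 exercise sessions in one arm and 9 social meetings in the other. The covariate is therefore bound up with allocation and sits badly with the stated intention-to-treat basis.

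The cost is analysis wording only, agreed before outcome data are examined. Every variable is already collected.

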**Fig. 1 Fig1:**
[figure not shown]
Consort flow diagram of recruitment and randomization

Participants from the EPIG will undergo an 18-week exercise intervention. The exercise sessions will be provided two times a week (each class approximately 1 to 1.5 h duration) and will be supervised by a qualified physiotherapist or an accredited exercise physiologist. Each session will consist of 5 to 10 min warm-up exercises, followed by 45 to 75 min on the equipment stations, and will conclude with 5 to 10 min of cool down exercises. The exercise classes will include 6 to 8 participants and will be circuit-based with the warm up and cool down exercises being performed in a group and the core session being carried out in training pairs. Participants will be performing exercises that focus on strength, balance, coordination, mobility and flexibility as detailed in Tables 1, 2, 3, 4 and 5. Exercisers will be paired in stations and an exercise session can include up to eight stations (See Table 6). The intervention program will be carried out at St Bernadette’s Community Respite House, with no cost to the participants.

**Table 1 Tab1:** Strength exercises to be performed using the senior exercise park with their respective levels of progression

Exercise	Description	Functional relevance	Progressions
Push-up bar	Participant pushes body up away from the bar and brings it down towards the bar.	Strengthens arms, back and core muscles.	Standing nearly perpendicular to the bar:
			Level 1 – Wide grip.
			Level 2 – Narrow grip.
			Level 3 – Wide grip standing on a 10cm high block*.
			Level 4 – Narrow grip, standing on a 10cm high block*
			Level 6 – Narrow grip, hand release.
			Level 7 – Narrow grip, front knee tucks.
			Level 8 – Narrow grip side knee tucks.
			Level 9 - Perform the push-ups with 1 hand. Hand on shoulder line.
Modified Pull-Ups	Participant pulls body up towards the bar.	Strengthens arms, back and core muscles.	Level 1–3 – Hands narrow (undergrip), increase distance from the bar (3 distances 3 distances determined by a line on the floor).
			Level 4–6 – Hands wide (undergrip) – increase distance from the bar (3 distances)
			Level 7–9 – Hands narrow (overgrip) – increase distance from the bar (3 distances).
			Level 10–12 – Hands wide (overgrip) – increase distance from the bar (3 distances).
			If the participant reaches RPE 4/10 again, the wooden 10-cm high block can be introduced on the exercise and all levels are repeated again.

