3	Balance Stool	Calf Raises + Finger Steps
4	Sit to Stand	Rounded Snake Pipe
5	Ramp + Net + Climb Through	Sharp Snake Pipe
6	Balance Beam	Hip extension
7	Stairs	Screws / Turners
8	Step-ups	Hip Abduction

Participants in the CG will be advised to continue with their usual daily activities and will be meeting the research team every two weeks to take part in some social activities (nine meetings of two hours duration over 18 weeks of intervention). Participants from both groups will be tested at the following timelines: baseline, at the end of the intervention period (18 weeks) and two months after that (26 weeks after intervention commencement).

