### Feasibility

As the senior exercise park initiative is a new concept to the Australian older community, feasibility will be assessed and will be defined as the number of participants recruited and retained over the recruitment period, overall adherence and seasonal adherence, safety and adverse effects and number of sessions cancelled due to unfavourable weather conditions. In addition, the qualitative data collected via interviews of EPIG participants will be taken into account for feasibility purposes as they might more clearly show participants’ perceptions of this kind of initiative.

Overall adherence to the exercise program will be defined by the number of sessions attended: 100 % adherence if participant attended 35 sessions or 9 sessions of social meetings. EPIG or CG participants’ participation and attendance will be recorded via a spreadsheet diary and will be collected respectively by the exercise supervisor of that participant on each specific session or by the principal researcher. Physical activity calendars will be used to monitor if EPIG or CG participants have participated in any other physical activities during their participation in the study. Reasons for participants missing sessions will be documented on the spreadsheet diary. Participants will be given a phone call in case they miss two consecutive sessions without any communication with any exercise supervisors.

Considering that the exercise sessions are held outdoors, this study intends to investigate if the participants’ adherence would be influenced by weather conditions during the four seasons in Melbourne. Seasonal adherence will be recoded as adherence over Summer (December to end of February), Fall (March to end of May), Winter (June to end of August) and Spring (September to end of November). Also, the number of sessions that were cancelled due to rainy, windy and excessively hot days (above 37 °C) will be recorded given that these conditions would potentially put participant’s safety and health in risk.

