### Fidelity monitoring

To assure that the core elements that contribute to the success of intervention studies will be correctly documented and can be successfully translated into community settings, a number of process measures will be used to document, track and enhance the fidelity of this project. Firstly, all exercise supervisors will receive a written exercise protocol manual to be followed in all sessions. Secondly, participants will have their attended sessions recorded by the supervising researcher to make sure that they are receiving nearly the same amount of exercise prescription at the end of the 18 weeks of exercise intervention. Participants who have missed more than eight sessions (for being unwell or away) at the end of the 18-week period will be asked to make up these missed sessions until they reach a minimum of 35 h (out of 50 expected hours) of exercise delivery. Finally, fidelity to treatment delivery will be monitored via the use of exercise cards (per participant) for the specific training date with further details of the participant’s performance and general suggestions for the next session (i.e. improve level of certain exercise, monitor pain, watch technique, etc.).

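### Number of sessions attended, measured after randomisation and on a different scale in each arm, is a covariate in the only stated outcome model, so the group comparison may not estimate the effect of assignment

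*Protocol article*

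**What the plan says.** The Data management and statistical analysis section opens with "All analyses will be conducted on an intention-to-treat basis". It then sets out one model, "Mixed linear modelling incorporating intervention and control groups at the baseline and two follow up time points", and specifies it "with the number of sessions attended and baseline physical activity level as covariates". That model serves everything: "Comparisons will be made for the primary outcome (BOOMER) and secondary outcomes". It is not labelled an adherence or dose analysis, no version without the attendance covariate is given, and no parameter (group, group-by-time, or adjusted mean at a visit) is named as the treatment effect.

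Attendance is counted differently in the two arms. For the exercise arm, the text after Fig. 1 says "The exercise sessions will be provided two times a week" for 18 weeks. For the control arm, the text after Table 6 gives "nine meetings of two hours duration over 18 weeks of intervention". The Feasibility section defines 100% as "adherence if participant attended 35 sessions or 9 sessions of social meetings". Fidelity monitoring adds a catch-up rule for the exercise programme, whose opening words are "Participants who have missed more than eight sessions (for being unwell or away) at the end of the 18-week period will be asked to"; the rest of that sentence calls for lost classes to be recovered up to a minimum number of hours.

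**The concern.** Sessions attended is not known at randomisation. It is how much of the assigned programme a person received, it is the route by which the park would work, and it is likely to be related to health, since the article itself names being unwell as a reason for missing sessions. Conditioning on it asks how two people with the same count would differ if one were in each arm.

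That comparison hardly exists here. A control can reach at most 9. An exerciser shares a count with a control only by attending 9 or fewer of 35. Someone who misses eight, the limit before make-up sessions are requested, still has 35 − 8 = 27, three times the control maximum. At equal counts the model compares exercisers who largely stopped with controls who attended, or it extrapolates.

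At stake is the primary conclusion. An effective programme could be reported as ineffective. If better attenders do better for other reasons, an ineffective programme could be reported as harmful.

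**Working it through.** **Inputs from the article.** Maximum attendance 35 and 9 (Feasibility). Effect size 0.5, 48 per group before dropout, alpha 0.05 (Sample size). Twice weekly for 18 weeks would be 36; the article uses 35, and the difference does not matter here.

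**Plan's own figure.** 48/(1 − 0.20) = 60 per group, as stated. I take 48 per arm as the analysed number. How 48 was obtained is a separate question.

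**Assumed, because the article gives no attendance distribution.** Mean attendance 70–90% of each arm's maximum, SD 10–20 percentage points, counts capped at the maximum, and 0% or 20% stopping early.

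**1. How closely the count tracks the arm.** With equal arms, r² = (D/2)² / [(D/2)² + V], where D is the difference in mean counts and V the average within-arm variance. At 80% and SD 15 points:
- exercise arm: mean 28, SD 5.25, variance 27.56
- control arm: mean 7.2, SD 1.35, variance 1.82
- D = 20.8 and (D/2)² = 108.16; V = (27.56 + 1.82)/2 = 14.69
- r² = 108.16/122.85 = 0.880, so r = 0.94 and 1/(1 − r²) = 8.4

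Capping the counts gives r = 0.945 and variance inflation 9.4. Over the whole assumed range r is 0.80–0.98 and inflation 2.7–28.

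**2. Precision of an adjusted between-arm contrast.** Without baseline adjustment, SE = √(2/48) = 0.204 SD and 0.5/0.204 = 2.45, so two-sided power is Φ(2.45 − 1.96) = 0.69. Multiplying the SE by √2.7 = 1.65 gives Φ(1.48 − 1.96) = 0.32. Multiplying it by 5.28 gives Φ(0.46 − 1.96) = 0.07.

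**3. Bias in follow-up ANCOVA.** The adjusted estimate is approximately the unadjusted one minus b × D, where b is the pooled within-arm slope of outcome on count.
- *True effect 0.5 SD, proportional to exercise sessions.* The slope is 0.5/28 = 0.0179 in the exercise arm and 0 in controls. b = 0.0179 × 27.56/(27.56 + 1.82) = 0.01675. Estimate = 0.50 − 0.01675 × 20.8 = 0.15 SD.
- *No effect, but better attenders do better by 0.3 SD per SD of attendance (assumed).* b = 0.3 × (5.25 + 1.35)/29.38 = 0.0674. Estimate = 0 − 0.0674 × 20.8 = −1.40 SD. With 0.26 SD per SD, and attendance of 28 (SD 5) and 7.2 (SD 1.5), b = 0.26 × 6.5/27.25 = 0.0620 and the estimate is −1.29 SD.

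**4. Which contrast is affected.** Simulation with 48 per arm, 80% attendance, SD 15 points and 1,500 replicates. Each cell gives the mean estimate in SD (rejection rate), without → with sessions in the model.

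| Treatment effect read from | True 0.5 SD, through sessions | No effect, better attenders do better |
|---|---|---|
| Follow-up ANCOVA at 18 weeks | 0.50 (0.85) → 0.17 (0.06) | 0.01 (0.05) → −1.40 (0.75) |
| Group-by-time, with sessions-by-time | 0.50 (0.78) → 0.15 (0.06) | 0.01 (0.06) → −1.38 (0.67) |
| Group main effect over all three visits | 0.34 (0.48) → 0.09 (0.06) | 0.00 (0.05) → −0.91 (0.37) |
| Group-by-time, sessions as main effect only | 0.50 (0.78) → 0.51 (0.80) | 0.01 (0.06) → 0.00 (0.05) |

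The last row is the exception. A covariate that is constant within a person cannot alter within-person change when the data are complete.

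**5. Coding.** As a percentage of each arm's maximum, 28/35 and 7.2/9 are both 80%. The correlation with arm is then about 0.01, and ANCOVA returns 0.50 with power about 0.80, and about 5% rejection under the null.

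**The case against.** The strongest reply is that the article plans a repeated-measures model with baseline as one of the time points, not a follow-up ANCOVA. In such a model the usual treatment effect is group-by-time, and listing a variable among the covariates most naturally means a main effect. On that reading the covariate is nearly harmless, as the last table row shows. This stands as a limit on the size of the problem. It does not clear the plan, because the article names no contrast, and the damaging ones fit its wording equally well.

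Secondly, the near-identity with arm depends on raw counts, and the Feasibility section already defines adherence on an arm-specific scale. That also stands as a limit. But the analysis section specifies a number of sessions, which points to raw counts. A percentage would still be a post-randomisation variable, and it is free of collinearity only while mean percentage attendance is similar in the arms.

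Thirdly, the attendance distribution and the link between attendance and outcome are assumptions. The figures are illustrations, not forecasts.

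A reader might go further and infer that the planned estimate cannot be intention-to-treat or cannot be interpreted at all. The documents do not support that. Everyone may still be analysed in the arm to which they were randomised, and one natural reading of the model leaves the treatment contrast intact. The defect is that conditioning on treatment received can change what is estimated; keeping all participants in the dataset does not undo that.

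**Conclusion.** The concern holds in conditional form. The article fixes a post-randomisation measure of treatment received in its only stated model for the primary and secondary outcomes, and nothing elsewhere in it corrects this. A separate analysis plan might, but the choice as published is a stated one, not an omission.

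With raw counts, any group main effect, visit-specific adjusted mean, follow-up contrast or sessions-by-time model ceases to estimate the effect of assignment. Under the attendance assumptions above, follow-up ANCOVA takes a true 0.5 SD effect acting through sessions to about 0.15 SD with power about 0.05. With no effect and an assumed attendance–outcome association, it gives about −1.3 to −1.4 SD with false rejection above 60%. With sessions as a main effect only and group-by-time as the treatment effect, complete-data results are essentially unchanged. Confidence is high that the covariate is misplaced; the size of the harm depends on a contrast and a coding that the article leaves open.

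**What to change.** Delete the number of sessions attended from the model for the primary and all secondary outcomes, and keep baseline physical activity, which is measured before allocation. State that the treatment effect is the group-by-time contrast at 18 weeks. If attendance or dose is of interest, report it as a separate, labelled exploratory analysis, for example dose-response within the exercise arm, with the caution that attendance is not randomised.

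This costs a change of wording in one section and needs no new data. Under the one specification where the covariate is harmless, it adds nothing to the treatment contrast, so removing it loses nothing.
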